#### Secondary outcomes

Self-reported symptoms of anxiety, depression, sleep disturbance, loneliness and experiences of bullying victimisation.

#### Exposures

Social media metadata, textual and imagery data and smartphone metadata.

Self-reported social media and smartphone usage.

#### Other measurements

Self-reported exposure to COVID-19, sociodemographic and clinical covariates and process evaluation data.

### Data analysis plan

#### Descriptive analysis

Individuals will be grouped into those that have had an episode of self-harm, and those that have not. Frequency distributions for different types of self-harm will be summarised, and individuals with multiple, versus a single episode of self-harm will be compared. Baseline sociodemographic and clinical descriptors will be presented for those that self-harm and those that do not. Patterns of social media and smartphone use will be explored using a mixed methods analysis and presented as a descriptive analysis.

#### Primary analysis

Patterns of social media and smartphone use will be identified and categorised into specific problematic exposure groups. This will be defined using a mixed methods analysis comparing social media and smartphone data in the 7 days leading up to a self-harm episode. Individuals who do not experience an episode of self-harm will be randomly matched with four cases, and the same relative date and time of exposure will be randomly matched.

Social media and smartphone use will be compared between self-harm cases and non-cases, including social media platform of use, duration of use, time of use and absence of engagement (reduced level of posting but passive presence online). For example, night-time use compared with similar use during the day will be compared by self-harm status.

A binary generalised linear model with a log link will be fitted to derive the relative risk of a prospective self-harm episode in relation to a characteristic pattern of social media and smartphone use in the 7 days prior to the episode. Known social and physical determinants of health associated with self-harm will be included to adjust for baseline effects. Missing data will be explored for patterns of missingness. Secondary analyses will explore potential mediating effects of anxiety, depression, sleep disturbance, loneliness and bullying.

The primary analysis population under investigation will include all participants with a post-baseline assessment of self-harm.

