**Methods and analysis:**

To study the mechanisms by which social media and smartphone use underpin self-harm in a clinical sample of young people, the Social media, Smartphone use and Self-harm in Young People (3S-YP) study uses a prospective, observational study design. Up to 600 young people aged 13–25 years old from secondary mental health services will be recruited and followed for up to 6 months. Primary analysis will compare real-world data in the 7 days leading up to a participant or clinician recorded self-harm episode, to categorise patterns of problematic usage. Secondary analyses will explore potential mediating effects of anxiety, depression, sleep disturbance, loneliness and bullying.

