Self-reported smartphone use	Including most frequently used apps, average duration of daily usage, and night-time access to a smartphone.	X						X
Smartphone Addiction Scale - Short Version (SAS-SV)^49^	Smartphone addiction will also be measured using the 10-item SAS-SV.^ 49 ^ Scores range between 10 and 60, with 31 and 33 representing a cut-off for smartphone addiction in adolescent boys and girls, respectively. The SAS-SV is a widely used and validated instrument which operationalises problematic smartphone usage.^50^	X				X		X
Social media data upload	Retrospective (ie, since the account was created) and prospective social media data will be uploaded by participants from their accounts on Facebook, Instagram, Snapchat, TikTok, Twitter and YouTube, including duration of usage (hours/min per day), timing of usage (diurnal/nocturnal posting), frequency of usage (visits to platforms per day), type of use and textual and imagery data.	X			X			X
Smartphone metadata extraction	Smartphone metadata will be extracted continuously for the duration of follow-up using the study software application, including intensity of usage by time of day, frequency and duration of incoming and outgoing telephone calls, frequency of incoming and outgoing text messages and length of time spent on software applications. For participants with Android phones, permissions will be set to enable the Android App Usage API to track daily statistics listed above. For iOS, low level system logs will be used to retrieve similar information as listed above, where iOS allows.	X	X	X	X	X	X	X
Electronic health records data extraction	Clinician recorded self-harm events, using a similar approach to Polling *et al,* 51 and other relevant clinical variables will be extracted from structured and free-text fields in EHR using the CRIS system. For participants who provide social media data, data will be extracted from the date of the first interaction on social media (or the date of the 13th birthday, whichever is later) to the end of the follow-up. For participants who do not provide social media data, data will be extracted from the date of the baseline assessment.	X						X

CRIS, Clinical Research Interactive Search; EHR, electronic health record.

**Table 3 T3:** Outline of data collection measures over the 6-month follow-up period related to secondary objectives and other measurements

Measure	Description	Data collected at:						
		Baseline	Month 1	Month 2	Month 3	Month 4	Month 5	Month 6

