#### Natural language processing and language analysis

In previous work by coauthor [name]’s team^30^ aggregates of both language and smartphone features were obtained at hourly intervals preceding an episode (administration of a mood form). These were used in linear and non-linear regression models for prediction of mood scores. Recent work by [name]’s team has developed natural language processing methods to identify changes in the mood of individuals over time through sequential analysis of 2-week user timelines on social media,^31^ and has shown that capturing such changes can be predictive of suicidality risk.^32^ The current protocol focuses on the 7-day window preceding a self-harm episode, making the above-mentioned research directly applicable to this work. While language features used in earlier work includes word embeddings (sentiment specific and others), n-grams, topics and lexica for sentiment, recent developments have shown the success of pretrained language models (eg, BERT from Devlin *et al*)^33^ in capturing information on mental health.^31 34^ The textual content of individuals posts will be represented using pretrained language models, combined with other smartphone data, to predict both moments of change and episodes of self-harm. Our earlier work on fusing heterogeneous features using multiple kernel learning,^30^ will provide useful baselines. Measurements of affective change both through our models for moments of change^31^ as well as more traditional measures of valence and affect^35^ will feed into the predictive models as well as the descriptive analysis. Models will be evaluated under robust cross validation settings to simulate as much as possible a real-world scenario and avoid overfitting.^36^

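### The problematic-use groups are defined from the windows before self-harm and then tested against self-harm in the same participants, so the relative risk is liable to bias away from 1 and the 5% level is not assured

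*Protocol article*

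**What the plan says.** The Primary analysis section of the protocol article sets out one sequence. Usage patterns are sorted into problematic exposure groups, which are "defined using a mixed methods analysis comparing social media and smartphone data in the 7 days leading up to a self-harm episode". The abstract describes the same step (the quotation stops one word short of the end of its sentence): "Primary analysis will compare real-world data in the 7 days leading up to a participant or clinician recorded self-harm episode, to categorise patterns of problematic".

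The same section continues: "A binary generalised linear model with a log link will be fitted to derive the relative risk of a prospective self-harm episode", with a characteristic pattern of use in the preceding 7 days as the exposure. Of the population it says: "The primary analysis population under investigation will include all participants with a post-baseline assessment of self-harm".

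Usage is to be compared between cases and non-cases on platform, duration, time of use and absence of engagement. Neither the number of patterns nor the rule for calling one problematic is given.

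Three other places bear on the point:

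- **Sample size calculation:** 22.5% self-harm without and 35% with problematic use in the previous week, 480 followed up, 86% power at 5% significance.
- **Natural language processing and language analysis:** "Models will be evaluated under robust cross validation settings to simulate as much as possible a real-world scenario and avoid overfitting". This concerns the prediction models of that section.
- **Table 2, SAS-SV row:** an instrument with fixed cut-offs, collected at baseline, month 4 and month 6.

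**The concern.** Objective 1 is to find patterns that characterise the week before self-harm. Objective 2 is to ask whether those patterns differ from use in young people without an episode. Looking at case windows is the natural way to do the first. The second needs an exposure whose definition did not depend on who became a case.

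As written, one body of data serves both. If a pattern is called problematic because it stands out in case windows, it will tend to be associated with self-harm in those participants even when use and self-harm are unrelated. The relative risk, its confidence interval and its p-value would then all be too favourable. Matched non-case windows do not remove this, since contrasting them with case windows is one way the selection can occur. Covariate adjustment does not remove it either.

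At stake are the main estimate for objective 2 and the meaning of the 5% level used to justify 480 participants.

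**Working it through.** **1. Reproduce the planned power.** Inputs from the Sample size calculation: p1 = 0.225, p2 = 0.35, N = 480, 5%. The plan gives neither the sidedness nor the exposed share; I assume two-sided and 240 per group.

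- Mean proportion: (0.225 + 0.35)/2 = 0.2875
- SE under no difference: √(2 × 0.2875 × 0.7125/240) = 0.0413
- SE under the alternative: √((0.225 × 0.775 + 0.35 × 0.65)/240) = 0.0409
- z = (0.125 − 1.96 × 0.0413)/0.0409 = 1.076, so power = 85.9%

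The stated 86% reproduces. It applies to one binary exposure fixed in advance. The planned relative risk is 35/22.5 = 1.56.

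**2. False-positive rate when the outcome picks the exposure.** The selection rule is not in the plan, so it is an assumption here and is varied. Common settings: no true effect, 480 participants, 150 cases (the plan's minimum), normally distributed usage features correlated 0.3. The candidate most over-represented in cases is labelled problematic and tested at two-sided 5% in the same data, with 4,000 replicates. Upper side only means that only high values may count as problematic; either side means that low values may too.

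| Features | Cut-points searched | Direction | False-positive rate | Median null RR |
|---|---|---|---|---|
| 1 | median only | upper side only | 5% | 1.00 |
| 1 | three quartiles | upper side only | 7% | 1.09 |
| 1 | three quartiles | either side | 11% | 1.19 |
| 4 | median only | upper side only | 9% | 1.13 |
| 4 | median only | either side | 19% | 1.21 |
| 4 | three quartiles | upper side only | 20% | 1.23 |
| 4 | three quartiles | either side | 40% | 1.32 |
| 8 | median only | upper side only | 16% | 1.19 |
| 8 | three quartiles | either side | 61% | 1.37 |

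Separate runs under the same rules differ by one or two percentage points and by 0.01 to 0.02 in the relative risk. For four candidates I therefore summarise as about 10 to 40% and 1.14 to 1.33.

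**3. Check by formula.** For four independent candidates at one cut, upper side only: 1 − 0.975^4 = 9.6%. For either side: 1 − 0.95^4 = 18.5%. Both agree with the table.

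**4. More candidates.** With one cut, upper side only, and correlation from 0.5 down to 0, the rate is 11 to 12% for 5 patterns, 17 to 23% for 10 and 25 to 40% for 20.

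**5. Separate derivation from testing.** Selecting in one random half and testing in the other gave about 5 to 6% in every setting. The cost is power. With 120 per group the two SEs are 0.0584 and 0.0579, so z = (0.125 − 1.96 × 0.0584)/0.0579 = 0.18 and power is 57%. Testing 320 participants (160 per group) gives 70%.

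**The case against.** The strongest reply is that selection on case/non-case contrast is partly read into the text. The groups could be formed by describing what is common in pre-episode windows, with non-cases brought in only afterwards. Simulated that way, with the most common pattern in case windows chosen and pattern prevalences spread from 20% to 60%, the null rejection rate was 4.9% for four patterns and 5.1% for eight. With equal prevalences it was 8% and 13%. This stands: the inflation depends on a rule that the article does not give. A reader might infer a definite figure, such as 40%, or that the 5% level certainly fails. The document supports neither. The upper figures need a search over several cut-points in both directions that the plan never states, and platform of use is categorical, so quartile cuts do not apply to it.

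Second, the article condenses a fuller protocol, and the exact definition, its lock date and any masking may be set out there. That is fair for operational detail. It does not change what the article does state: the groups are defined from pre-episode data, and the model is fitted in everyone with a post-baseline assessment.

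Third, the study calls itself one of the first attempts to explore these patterns, and 5% appears only in sample size planning. This makes an exploratory label a legitimate remedy. It does not fit alongside an unqualified 86% power at 5% significance.

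Fourth, a categorisation that rests partly on human judgement is hard to repeat across folds, and a half split is expensive. Both points stand and shape the fix.

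It is also tempting to substitute the SAS-SV, since the article says "The SAS-SV is a widely used and validated instrument which operationalises problematic smartphone usage". That does not work. It is collected only at baseline, month 4 and month 6, its stated cut-offs are for adolescents while the cohort runs to age 25, and it does not capture use in the 7 days before an episode.

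**Conclusion.** The point holds as a risk created by the stated procedure, not as a proven error rate. The exposure groups are defined from the windows before self-harm, and their relative risk is then estimated in the same participants with no safeguard stated for that model. The relative risk is therefore liable to be biased away from 1, and the 5% level is not assured.

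With no true effect and 480 participants, the false-positive rate is near 5 to 7% for one candidate at a single cut and about 10 to 40% for four, and it rises with more. The median null relative risk for four is about 1.14 to 1.33, a material part of the planned 1.56. These figures assume a single hard selection of the candidate most over-represented in cases. A theory-led definition would inflate less; freer tuning would inflate more.

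Objective 1 is descriptive and unaffected. A reader might conclude that objective 2 cannot be answered at all. That goes too far, because the same data can answer it once the definition is separated from the outcome. The power arithmetic itself is correct for a fixed exposure.

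**What to change.** Keep the outcome-informed search for patterns as description under objective 1. For the relative risk under objective 2, do one of the following and say which:

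1. **Preferred.** Derive and lock the usage categories from all case and matched non-case windows with case status masked, or fix the definitions before linkage to outcomes. The lock should precede any unmasked reading of case windows, including the thematic analysis. If several categories result, name the contrast to which the 5% applies. The cost is wording and sequencing: no new data, 480 participants kept, and the planned 86% kept on the same assumption of equal exposed and unexposed groups.
2. **Where categories can be derived by algorithm.** Use participant-level cross-fitting: derive in all folds but one, classify the held-out participants, and pool. This costs some precision and more analysis work. A simple half split is not advised, since power falls to about 57%.
3. **If neither is done.** Label the relative risk exploratory and withdraw the 5% significance and 86% power statement.

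Do not make the SAS-SV the replacement primary exposure.

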## Methods and analysis

### Study design

This study is a prospective 6-month cohort study and has been reported according to the Strengthening the Reporting of Observational Studies in Epidemiology checklist for cohort studies (see online supplemental additional file 1) (protocol V.1.4, 21/07/2022).

10.1136/bmjopen-2022-069748.supp1Supplementary data

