### Sample size calculation

In a recent national community survey, the reported annual age-sex incidence of self-harm for young people aged 16–18 years old was 36.4% (95% CI 22.4 to 52.2) for men and 43.5% (95% CI 35.5 to 51.7) for women.^3^ Based on uptake of SLaM C4C patient research participation register, we estimate that if 600 young people consent to take part, 480 will be followed up during a 6-month period, resulting in at least 150 with an episode of self-harm. Using the most conservative estimates, if approximately 22.5% of those who do not display characteristic problematic patterns of social media usage (or smartphone usage) have an episode of self-harm and this increases to 35% in those identified with problematic usage in the previous week, we expect 86% power to detect a 12.5% increase in self-harm at 5% significance, assuming 480 young people are followed up.

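### The primary analysis does not reconcile four-fold matching with an all-participant log-link relative risk; if the matching sets the case mix, the fitted ratio is not the cohort relative risk

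*Protocol article*

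**What the plan says.** The protocol article makes three statements under Primary analysis that bear on this point.

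- Matching: "Individuals who do not experience an episode of self-harm will be randomly matched with four cases". A non-case's exposure window takes its relative timing from the match.
- Model: "A binary generalised linear model with a log link will be fitted to derive the relative risk of a prospective self-harm episode". The exposure is the usage pattern over the preceding week. No weights are mentioned.
- Population: "The primary analysis population under investigation will include all participants with a post-baseline assessment of self-harm".

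The Study design section says "This study is a prospective 6-month cohort study". The Sample size calculation compares two risks in 480 people followed up. For the group without problematic usage it supposes that "approximately 22.5% of those who do not display characteristic problematic patterns of social media usage (or smartphone usage) have an episode of self-harm". The risk it supposes for the other group is 35%. It expects at least 150 people with an episode and 86% power. The article does not say how the matched windows relate to the full population, or how many rows each person contributes to the model.

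**The concern.** A log-link binary model estimates a ratio of fitted case proportions. In an intact cohort those proportions are risks, so the ratio is a relative risk. If a matching factor decides how many non-case rows stand against each case, the proportions reflect that choice and the ratio changes with it. The odds ratio does not change in this way, but it is not the measure the plan names.

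The two sentences on matching and population therefore lead to different primary estimates from the same people. An analyst could follow either one and claim to have followed the protocol.

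**Working it through.** **Inputs.** Risks of 22.5% and 35%, 480 followed up, at least 150 cases, 86% power and 5% significance all come from the Sample size calculation. The exposed/unexposed split is not stated. I assume 240/240.

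**Reproducing the plan's figure.** Two-sided test of two proportions, 240 per group:

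- pooled risk = (0.225 + 0.35)/2 = 0.2875
- standard error under the null = √(0.2875 × 0.7125 × 2/240) = 0.0413
- standard error under the alternative = √((0.225 × 0.775 + 0.35 × 0.65)/240) = 0.0409
- power = Φ((0.125 − 1.96 × 0.0413)/0.0409) = 85.9%

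This matches the stated 86%. The power statement is thus an unmatched comparison of two cohort risks. The split gives 138 cases, somewhat below the 150 quoted.

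**Expected cohort table.** Exposed: 84 cases, 156 non-cases. Unexposed: 54 cases, 186 non-cases. In total there are 138 cases and 342 non-cases, or 2.48 non-cases per case.

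- Relative risk = (84/240)/(54/240) = 0.35/0.225 = 1.556
- Odds ratio = (84 × 186)/(54 × 156) = 1.855

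**Log-link ratio when the mix changes.** Non-case rows are rescaled without regard to exposure, so their exposure odds stay at 156:186.

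| Reading | Non-case rows, exposed/unexposed | Fitted proportions | Ratio |
|---|---|---|---|
| Each person once | 156 / 186 | 0.350 / 0.225 | 1.556 |
| Four non-cases per case (552 rows) | 251.8 / 300.2 | 0.2502 / 0.1525 | 1.641 |
| Four windows per non-case (1,368 rows) | 624 / 744 | 0.1186 / 0.0677 | 1.753 |

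The odds ratio is 1.855 in every row.

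**Dependence on the assumed split.** The third row does not depend on it: [0.35/(0.35 + 4 × 0.65)] / [0.225/(0.225 + 4 × 0.775)] = 1.753 at any split. The second row does: with 20% exposed it is 1.609.

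**Feasibility.** With at least 150 cases among 480, at most 330 non-cases exist, or 2.2 per case. Four distinct non-cases per case would need 600. Four windows for each of 330 non-cases is feasible. It gives 1,320 non-case rows, and the apparent overall risk falls from 150/480 = 31% to 150/1,470 = 10%.

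**Weighting.** Giving each of the four windows a weight of 1/4 restores 624/4 = 156 and 744/4 = 186, and hence 1.556.

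**The case against.** The strongest defence is that nothing is subsampled. A non-case has no episode to anchor a 7-day window, so the matching may serve only to lend it a date. The section names all participants as the population, the design is a cohort, and the power calculation compares cohort risks. If each person enters once, the log-link model returns the cohort relative risk for an exposure treated as a characteristic of the person. That stands. What it does not explain is what the factor of four is for.

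Several stronger readings are tempting but are not supported:

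- A reader might infer that no relative risk can be obtained after matching. The whole cohort is enumerated, so sampling fractions are known and weights recover it.
- A reader might infer that the estimate reflects the sampling ratio instead of the association. With no association the ratio is 1 at any mix, so the null value is unaffected.
- A reader might take the wording to mean one non-case kept per four cases, which would pull the ratio down to 1.135. That would keep about 35 of 342 non-cases, and nothing in the article says the rest are discarded.
- A reader might fault the model for having no matched-set term or for its standard errors. A condensed article may leave these to an analysis plan that is not shown.
- A reader might object that an odds ratio with never-case controls (1.855) overstates the relative risk. The plan does not propose to report an odds ratio.

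**Conclusion.** The point holds conditionally. As written, the matching sentence and the all-participants sentence are not reconciled. On the readings computed here in which the factor of four sets the row mix, the unweighted log-link model does not deliver the stated relative risk. On the protocol's own risks, the feasible reading (four windows per non-case) gives 1.75 against 1.56, about 13% too high (1.753/1.556 = 1.127). The four-controls-per-case reading gives 1.64, about 5% too high, but cannot be carried out with distinct people.

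These are expected values. They treat exposure as a person-level characteristic and assume that non-case rows are drawn independently of exposure and are unweighted. The cohort relative risk of 1.56 and the figure of 1.75 do not depend on the exposure split. The 1.64 does, and so does the reproduction of the power. If each person enters once, or rows are weighted back, the distortion disappears.

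**What to change.** State how the matched windows relate to the all-participants population and how many rows each person contributes, and make the effect measure fit that sampling. There are two routes.

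(a) Keep the log-link relative risk. Enter every participant once, with one randomly assigned index window for each non-case, and remove the factor of four. Alternatively, keep several windows per non-case, weight them by the inverse sampling fraction, and use a robust variance clustered on participant. This agrees with the cohort design and with the stated power basis.

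(b) Keep matched sets. Draw controls from participants who are under observation and episode-free at the case's index time, fit conditional logistic regression on the matched sets, and report an odds ratio interpreted as a rate ratio, not a relative risk. The power basis should then be restated to match.

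Both routes use the data already planned. The cost is a change of wording and slightly more analysis work; under (b) the effect measure also changes.

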**Trial registration number:**

NCT04601220.

Strengths and limitations of this studyThe Social media, Smartphone use and Self-harm in Young People (3S-YP) study uses a novel prospective, observational strategy to investigate the patterns of real-world social media and smartphone usage prior to episodes of self-harm in a clinical youth sample.Co-production with youth experts by experience, including coauthor ([name]), a leading national UK youth mental health charity—YoungMinds, and a steering group comprising of experts in the field of self-harm and suicide prevention will ensure acceptability and relevance, as well as facilitate dissemination and impact.Due to the online nature of the study, participants need to be able to independently engage with the digital tools and study documentation that is only available in the English language.The flexible approach to participation regarding which data young people choose to share, will ensure our methods are acceptable and promote autonomy among participants, though it will increase the risk of missing and inconsistent data which could compromise the validity of the results and interpretations made.Mixed model analyses, state-of-the-art natural language processing methods combined with thematic analysis, will be used to analyse social media metadata, textual and imagery data and smartphone metadata.

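### The one-to-four matching can bring the same non-case into the primary analysis several times, and the stated log-link model names no allowance for repeated use of a person

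*Protocol article*

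**What the plan says.** In the protocol article, Data analysis plan, Primary analysis, the matching rule reads: "Individuals who do not experience an episode of self-harm will be randomly matched with four cases". The same sentence adds that the relative date and time of exposure are matched as well. The model is given two paragraphs later: "A binary generalised linear model with a log link will be fitted to derive the relative risk of a prospective self-harm episode". Adjustment is for known determinants of self-harm. No matched-set term, person effect or variance estimator is named. The section closes by defining the analysis population in terms of participants with a post-baseline self-harm assessment.

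The strengths and limitations list describes the analysis differently: "Mixed model analyses, state-of-the-art natural language processing methods combined with thematic analysis, will be used to analyse social media metadata". The Descriptive analysis and Primary analysis sections speak of mixed methods, which is a different thing.

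The Sample size calculation supplies the counts: "if 600 young people consent to take part, 480 will be followed up during a 6-month period". Among them it expects no fewer than 150 cases. It ends with "we expect 86% power to detect a 12.5% increase in self-harm at 5% significance, assuming 480 young people are followed up".

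**The concern.** Four matched cases supply up to four index dates, so one non-case may be observed in up to four separate weeks. Weeks from the same person are likely to resemble each other. An ordinary binary model that receives these weeks as separate rows counts them as separate people. The standard error of the primary relative risk then comes out too small, and a test declared at 5% rejects more often than that.

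The article fixes both the matching ratio and the model family. As written, nothing in the second answers the repeated use of people that the first can create. Reversing the direction of the match, to the more usual four controls per case, does not remove the reuse at the stated ratio.

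**Working it through.** **1. The plan's own figure.** Inputs from the Sample size calculation: 480 followed up, risks of 22.5% and 35%, 5% significance. Assumed: equal exposure groups of 240 and a two-sided test, neither of which is stated.
- Pooled SE = √(2 × 0.2875 × 0.7125 / 240) = 0.0413.
- Unpooled SE = √((0.225 × 0.775 + 0.35 × 0.65) / 240) = 0.0409.
- z = (0.125 − 1.96 × 0.0413) / 0.0409 = 1.08, so power is 85.9%.

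The stated 86% reproduces, with each participant counted once.

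**2. How often people are linked.** With 150 cases there are 480 − 150 = 330 non-cases. Because the plan says at least 150 cases, 330 is a maximum.
- As written (each non-case to four cases): 330 × 4 = 1,320 links, and 1,320 / 150 = 8.8 per case.
- Reversed (four non-cases per case): 150 × 4 = 600 control windows, and 600 / 330 = 1.8 per non-case.
- Matching without reuse would allow at most 330 / 150 = 2.2 controls per case.

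**3. Effect on the standard error: each case once, four windows per non-case.** This gives 150 + 1,320 = 1,470 rows. Let *a* and *b* be exposed and unexposed case rows, and *c* and *d* exposed and unexposed non-case rows. The usual variance of the log relative risk is

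V = 1/a − 1/(a+c) + 1/b − 1/(b+d).

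Under no effect, non-case rows contribute the share 150/1,470 = 0.102 of V. Four windows with within-person correlation ρ multiply that part by 1 + 3ρ. Hence

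true SE / reported SE = √(1 + 3ρ × 0.102).

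| ρ (assumed) | SE ratio | Error rate at nominal 5%, normal approximation |
|---|---|---|
| 0 | 1.00 | 5.0% |
| 0.3 | 1.04 | 6.1% |
| 0.5 | 1.07 | 6.8% |
| 0.8 | 1.12 | 7.9% |
| 1 | 1.14 | 8.6% |

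Simulation under no effect with 50% exposed gave 6.1%, 7.1% and 8.0% at ρ = 0.3, 0.5 and 0.8. Under the plan's assumed effect (35% against 22.5%) the ratio is 1.07 at ρ = 0.5 and 1.14 at ρ = 1. With 30% exposed it is 1.09 and 1.17.

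**4. Other layouts.**

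| Layout | SE ratio | Error rate |
|---|---|---|
| One row per participant (480 rows) | 1.00 | nominal |
| Four non-cases per case, with reuse | not tabulated | 6.4%, 7.1%, 7.9% at ρ = 0.3, 0.5, 0.8 |
| One non-case plus four case rows per set (1,650 rows) | about 1.65–1.7 | 23–25% |
| All 1,320 case/non-case pairs | about 2.2–2.5 | 38–47% for ρ from 0 to 1 |

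The last two rows require the same case window to be entered many times as if it were new data.

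**The case against.** The strongest reply is that the article never says rows are treated as independent. It names a family and a link. The variance estimator is detail that a condensed article may leave to the full protocol or analysis plan, and a log-link model with participant-clustered errors fits the text word for word.

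Nor does the article say how many windows a non-case contributes. The population is defined by participants, and the power calculation reproduces with one row each. One randomly chosen index date per non-case is therefore a fair reading, and under it nothing is wrong. This part of the reply stands, and it makes the point conditional.

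A reader might infer from 8.8 links per case that each case enters the model about nine times, so that the error rate exceeds 40%. The document does not support that. Linking a case to several non-cases to set their dates does not duplicate the case's row, and its 7-day window is the same each time.

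A reader might also see a flat contradiction between the mixed-model wording and the primary model. That is too strong. The wording sits in a summary list covering all the social media and smartphone data, and it may be loose phrasing for mixed methods. It needs aligning, but it does not show that two primary models were specified.

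What the reply does not remove is the mismatch within one section: a one-to-four rule that literally yields repeated windows, next to a model with no stated means of handling them. One row per participant is compatible with the text but not stated, and it leaves the factor of four with little evident purpose.

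**Conclusion.** The point holds in conditional form. If the matched windows of a non-case enter as separate rows and each case enters once, the true standard error is about 5 to 12% larger than the reported one; put the other way, the reported one is roughly 4 to 10% too small. The 5% test then runs at about 6 to 8%. This rests on 150 cases and 330 non-cases from the plan, an assumed within-person correlation of 0.3 to 0.8, 50% exposed, and an unadjusted comparison. At the extreme of perfect correlation the ratio is about 1.14 (1.17 with 30% exposed).

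There is no narrowing with one row per participant. The much larger error rates belong to layouts with duplicated case rows, which the article does not describe. The severity is moderate: the distortion is modest on the literal reading, but the open choice affects the primary test and is nearly free to settle.

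**What to change.** In the Primary analysis section, state that each case window enters once, and then choose one of two routes:
- assign each non-case a single index window; or
- keep several windows per non-case and fit the model with participant-level cluster-robust standard errors, or a person random effect, in a way that takes account of the matching.

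Of the two variance options, clustering is the safer. Case status is the same in every row of one person, so a person random effect in a model for case status has little to identify it.

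Clustering repairs the standard error only. The number of rows per non-case also sets the share of cases, and with it the relative risk: with the plan's risks and 50% exposed, 150 cases and 330 non-cases give 1.53 with one row each and 1.74 with four windows per non-case. The single-window route avoids both effects.

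Reword the strengths and limitations list so that its mixed-model phrase names the same analysis, or says mixed methods if that is meant.

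The cost is a few sentences and, on the second route, one variance option in the software. No new data are needed. The downside is a slightly wider confidence interval.
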